**RESPONSIBLE PARTY**

[name] MD.

*This study was discussed in the Multidisciplinary Treatment Team for Thoracic cancer, approved by the Institutional Review Board of Fudan University Shanghai Cancer Center, and registered in Clinicaltrial.Gov under number NCT01807936.*

1. **Background:**

Esophageal carcinoma is an aggressive disease with a poor prognosis. Surgical resection with radical lymphadenectomy remains the basic method of management of this malignancy. Lymph node metastasis is one of the important factors in predicting the prognosis of patients with esophageal carcinoma, but the extent of lymph node dissection is still in debate. In the randomized trial of transhiatal compared with transthoracic esophagectomy for adenocarcinoma from the Netherlands, patients with positive lymph nodes potentially benefited from transthoracic esophagectomy with radical lymphadenectomy) (Hulscher JB, N Engl J Med. 2002). However, cervical LNM are common in esophageal cancer, with the incidence more than 20%. To improve the survival, three-field lymphadenectomy was developed to remove all potentially positive lymph nodes in the neck, mediastinum and upper abdomen. However, the value of three-field lymphadenectomy remains controversial due to the lack of prospective evidence. To date, only 2 randomized trials compared three-field lymphadenectomy and two-field lymphadenectomy, but the results are conflicting and the studies underpowered (Kato H, Ann. Thorac. Surg. 1991; Nishihira T, Am. J. Surg. 1998.)

1. **Purpose:**

The purpose of this study is to test two different extents of lymphadenectomy (Cervical-thoracic-upper abdominal three-field lymphadenectomy and thoracic-upper abdominal two -field lymphadenectomy) for patients with thoracic middle and lower esophageal cancer. This research is being done to see whether one extent of lymphadenectomy is superior than the other with better long-term outcome and acceptable postoperative short-term outcome or not.

1. **Trial:**
2. Allocation: Randomized (sealed envelope method).
3. Endpoint Classification: Efficacy Study.
4. Intervention Model: Parallel Assignment.
5. Masking: Open Label.
6. Primary Purpose: Treatment.
7. Single-institutional.
8. **Study protocol:**

[figure not shown]

Figure 1. Screening, randomization, follow-up and explorative sequencing of the patients.

**4.1 Estimated Enrollment:** 400.

PASS (power analysis and sample size software) were used for sample size calculation. Previous data indicated a 15% difference in 5-year survival between two-field lymphadenectomy (30%) and three-field lymphadenectomy (45%). With a three-year accrual and an estimation of 10% loss of follow-up, 200 patients per study arm were necessary, using 80% statistic power.

**4.2 Randomization:**

Randomization, by the sealed envelope method, took place on the morning of planed surgery day. Sealed envelopes were prepared and provided by the Department of Biostatistics, Fudan University.

**4.3 Study Start Date:** March 2013

1. **Study Completion Date:** December 2019
2. **Primary Completion Date:** November 2016

**4.4 Surgery and postoperative treatment.**

Surgery was performed by consultant thoracic surgeons who had performed at least 50 esophagectomies each year. Esophageal resection specimens were histopathologically assessed by experienced pathologists using a standardized protocol in which site and size of the primary cancer, sample margins and tumor differentiation were recorded in addition to presence of lymphovascular invasion. All lymph nodes resected were labeled for pathologic examination according to the anatomical sites.

**Three-field lymphadenectomy:**

The patient is placed supine initially. Through an upper midline abdominal incision, gastric tubulization is completed and a feeding jejunostomy is performed. Meanwhile, cervical lymphadenectomy is performed through a collar incision using the technique reported before (Yajima S, Int. J. Surg. Oncol. 2012). Next, the patient is positioned in left lateral decubitus and a right thoracotomy with a muscle-sparing incision is made in the fourth intercostal space. After ligating and dissecting the azygos vein, the esophagus is resected. Subsequently, the gastric tube is delivered into the thorax and a circular stapled end-to-side esophagogastric anastomosis is fashioned in the upper mediastinum. In addition, a nasogastric tube is also positioned in the gastric tube to prevent vomiting and acute gastric tube distension.

Following lymph nodes are resected during cervical lymphadenectomy: Cervical paraesophageal lymph nodes, supraclavicular nodes (no. 104).

Following lymph nodes are resected during mediastinal lymphadenectomy: Upper paraesophageal nodes, nodes along the bilateral recurrent nerves, subcarinal nodes, middle paraesophageal nodes, bilateral hilar lymph nodes, lower paraesophageal nodes, posterior mediastinal lymph nodes, and diaphragmatic nodes.

Following lymph nodes are resected during upper abdominal lymphadenectomy: Paracardial nodes, lesser curvature nodes, greater curvature nodes, left gastric, common hepatic nodes and celiac lymph nodes.

**Two-field lymphadenectomy:**

The patient is placed supine initially. Through an upper midline abdominal incision, gastric tubulization is completed and a feeding jejunostomy is performed. Next, the patient is positioned in left lateral decubitus and a right thoracotomy with a muscle-sparing incision is made in the fourth intercostal space. After ligating and dissecting the azygos vein, the esophagus is resected. Subsequently, the gastric tube is delivered into the thorax and a circular stapled end-to-side esophagogastric anastomosis is fashioned in the upper mediastinum. In addition, a nasogastric tube is also positioned in the gastric tube to prevent vomiting and acute gastric tube distension.

Following lymph nodes are resected during mediastinal lymphadenectomy: Upper paraesophageal nodes, nodes along the bilateral recurrent nerves, subcarinal nodes, middle paraesophageal nodes, bilateral hilar lymph nodes, lower paraesophageal nodes, posterior mediastinal lymph nodes, and diaphragmatic nodes.

Following lymph nodes are resected during upper abdominal lymphadenectomy: Paracardial nodes, lesser curvature nodes, greater curvature nodes, left gastric, common hepatic nodes and celiac lymph nodes.

**Postoperative treatment:**

Patients in both groups received similar postoperative treatment. Patients were extubated at the end of the procedure if physiologically stable, and were then admitted to the intensive care unit and discharged the next day to a thoracic surgery ward. In the first 3 days after surgery, patient-controlled epidural analgesia was the main postoperative pain control system. On postoperative day (POD) 1, patients were encouraged to move out of bed, and enteral nutrition was commenced via the feeding tube. Contrast swallow, not routinely but optionally, was performed on POD 5 or 6. Patients were started on sips of clear liquids on POD 6 and soft solid foods on POD 7, and discharged routinely on POD 7 or 8.

**4.5 Patients.**

**Ages Eligible for Study:** 18 Years to 75 Years

**Genders Eligible for Study:** Both.

**Healthy Volunteers:** No.

**Preoperative evaluation:**

Oncological evaluation included upper GI endoscopy with histologic examination, upper GI barium swallow, computerized tomography of the chest and upper abdomen, and ultrasound of the cervical region. Pulmonary and cardiac functions were also performed to assess the medical operability.

***Inclusion Criteria:***

1. Patients with histologically proven esophageal cancer
2. Patients with cT1-T3/N0-N1 mid or distal third (inferior to carina and 3cm superior to cardia ) operable esophageal lesion. Staging investigations including esophagogastroscopy, chest and abdominal CT scan, barium swallow and selective endoscopic ultrasonography showing no evidence of invading adjacent structure such as spine, bronchus, pericardium, descending aorta and without enlarged cervical and celiac nodes (diameter of short axis greater than 1.5cm) measured at CT scans.
3. Karnofsky performance status greater than or equal to 80%
4. Pulmonary and cardiac function must be acceptable for surgery according to institutional standards.
5. Acceptable hepatic, renal and bone marrow function

***Exclusion Criteria:***

1. Patients with low performance status (Karnofsky score <80%)
2. Past history of malignancy
3. Stage investigations indicating unresectable advanced disease (T4 or M1a,M1b)
4. Patients with any other serious underlying medical condition that would impair the ability of the patient to receive or comply with protocol treatment
5. Chemo and/or radiotherapy before surgery
6. Patients medically unfit for surgical resection
   1. **Data collection**

All collected data will be entered into a statistical software package for subsequent analysis.

- 1. **Postoperative treatment and follow-up**

Postoperative adjuvant treatment was given according to the postoperative pathological findings:

1. Radio-therapy was performed for patients with T3/4 tumors, or positive resection margins.
2. Chemo-therapy was performed for patients with positive lymph nodes.

Patients will be followed up every three months for the first two years and every six months for the third to fifth years and annually thereafter. A detailed history and clinical examination and CT scan, barium swallow and ultrasound will be done routinely on every follow up. Patients were seen either at our outpatient’s clinic or by telephone interview.

**5. Outcomes and measures:**

**5.1 Primary Outcome Measures:**

1. Overall survival: Time form randomization to the death due to any cause.

**5.2 Secondary Outcome Measures:**

1. Disease free survival.

Time from randomization to the first recurrence (locoregional, hematogenous, and others) or death from any cause.

1. Postoperative morbidity and mortality.

Hospital death defined as any death during hospital stay.

Postoperative complications included:

1. Anastomotic leak: Identified clinically or radio-graphically,
2. Respiratory complications: Clinical manifestation of pneumonia or bronchopneumonia confirmed by CT scan
3. Cardiovascular complications: Persistent arrhythmia requiring medical treatment
4. Chylothorax: Appearance of milky fluid from the thoracic drains after onset of enteral nutrition
5. Wound infections: Wound opened and daily bedside dressing is needed.
6. Delayed gastric emptying: Delayed oral food intake and confirmed by contrast swallow.
7. Pleural effusion: A thoracentesis was need.
8. Recurrent nerve injury: Hard to define, and recorded according to the change compared with the voice before surgery identified by patient and surgeon in charge.
9. Locoregional recurrence and recurrence pattern.

Recurrence were classified as locoregional (at the site of the primary tumor, the anastomotic site, or the lymph node), hematogenous, and other.

1. **Statistical analysis plan**

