**Secondary outcomes**

1. **Disease-free survival**，calculated from the time of randomization to date of first recurrence or death from any cause. Disease-free survival will be compared 3 years after the recruitment.
2. Perioperative morbidity and mortality, and oncologic efficacy will be compared when the last patient discharged.
3. Locoregional recurrence and recurrence pattern will be compared 3 years after the recruitment.

All data analyses will be performed with the statistical package SPSS. A *P* value of <0.05 is considered statistically significant.

- 1. Chi-square or Fisher’s exact test will be used to compare categorical data.
  2. Student’s t-test or the Mann-Whitney U test will be used for continuous data.
  3. The Kaplan-Meier method will be used to estimate survival, and the log-rand test will be used to determine significance.
  4. Multivariate Cox regression analysis will be used to identify the risk factors related to overall survival. Multivariate Logistic regression analysis will be used to identify the risk factors related to cervical lymph nodes metastasis.

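### Postoperative mortality is defined only as in-hospital death while routine discharge is on day 7 or 8, so the window is short and ends at a post-randomisation event

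*Protocol*

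**What the plan says.** Protocol section 5.2 lists "Postoperative morbidity and mortality" among the secondary outcomes. The one definition of death beneath it is "Hospital death defined as any death during hospital stay", followed by eight defined complications. No number of days is attached to the death definition.

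Section 4.4 (Postoperative treatment) states that patients were "discharged routinely on POD 7 or 8". The same paragraph opens with "Patients in both groups received similar postoperative treatment", so one discharge schedule is described for both arms.

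The statistical analysis plan section of the protocol (Secondary outcomes) sets the time of the comparison: "Perioperative morbidity and mortality, and oncologic efficacy will be compared when the last patient discharged".

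Three other places bear on the point:

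- The Trial section records "Masking: Open Label".
- The description of three-field surgery adds a neck dissection: "Meanwhile, cervical lymphadenectomy is performed through a collar incision".
- The follow-up text, printed after the exclusion criteria, says "Patients will be followed up every three months for the first two years".

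**The concern.** The stated purpose of the trial is to learn whether one extent of dissection gives better long-term results with acceptable short-term results. Early mortality is an obvious part of the second half of that question. Under the definition given, a patient who goes home on day 8 and dies on day 20 is not a postoperative death, while a patient who is still on the ward on day 20 and dies is one.

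Two weaknesses follow. The window is short for a patient who recovers routinely. Its end is also not set by the calendar. It is set by discharge, which follows randomisation, depends partly on clinical judgement, and is decided by staff who know the arm. If stay differed between arms for any reason, the arms would be watched for different lengths of time, and the arm with the longer stay would have more opportunity for a death to be counted. A fixed window removes that possibility whichever way stay might differ.

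**Working it through.** The plan gives no figure to reproduce on this point. It states no expected early mortality and no length of stay by arm, and its 200 patients per arm were derived for overall survival and do not enter here. The check is therefore mainly a comparison of the texts.

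**1. Is any fixed window defined?** Section 5.2 defines hospital death only. The Secondary outcomes text of the statistical section refers to perioperative mortality without defining it further. Overall survival (section 5.1) counts all deaths but has no early time point. So in-hospital death is the only operating definition of short-term mortality.

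**2. How long is the window?** It runs to day 7 or 8 for a routine course. The days left outside it, set against the two usual fixed windows, are:

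- 30-day window: 30 − 8 = 22 to 30 − 7 = 23 days
- 90-day window: 90 − 8 = 82 to 90 − 7 = 83 days

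These are days, not deaths. They apply to patients who leave on schedule. A patient with a serious complication would probably stay longer and be observed longer.

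**3. Could the window differ by arm?** The trial is open label, one arm adds a neck dissection, and discharge comes after randomisation, so it could. Section 4.4 describes similar care and one discharge schedule for both arms, and no stay by arm is given. The text neither shows a difference nor protects against one.

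**4. Do readmission deaths count?** The definition speaks of hospital stay without limiting it to the first admission. Either reading is possible.

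**5. Are the data for a fixed window already collected?**

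- Overall survival needs the date of death from any cause, counted from randomisation (section 5.1).
- Randomisation takes place on the morning of the planned operation (section 4.2). For a patient operated on that day, days from randomisation and days from surgery are the same.
- The first three-monthly contact falls at about 3 × 365.25 / 12 = 91 days. The protocol does not say whether this runs from surgery or from discharge. If from discharge on day 7 or 8, it falls at about 91 + 7 = 98 to 91 + 8 = 99 days after surgery. In either case vital status at day 90 is known from that contact.

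No new visit or data item is needed.

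**The case against.** The strongest reply is that no death is lost to the trial. Overall survival and disease-free survival both include death from any cause from the day of randomisation, so 30- and 90-day mortality can be read from the same data. In-hospital death is also a recognised endpoint. Here it is one part of one secondary outcome, and eight complications are reported beside it. A separate statistical analysis plan, not available for this review, might add a fixed window.

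Much of this stands. The gap lies in what is defined and compared, not in what is collected, and short-term safety does not rest on the death count alone. But the protocol itself fixes both the definition and the time of comparison. A log-rank test over the whole of follow-up does not isolate early deaths, so overall survival does not answer the short-term question.

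A reader might infer three stronger points that the text does not support.

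- **That neck dissection lengthens stay, so the arms are in fact observed for different times.** No length of stay by arm is given, and section 4.4 describes one schedule for both. This is a possibility only.
- **That deaths during readmission are excluded.** The wording leaves this open.
- **That comparing at the last discharge is a second flaw.** Under an in-hospital definition the outcome is complete for every patient at that moment, so section 5.2 and the statistical section agree. The timing needs to move only if the definition changes.

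**Conclusion.** The point holds as a weakness of definition in a secondary safety outcome. Short-term mortality is observed for about one week in a routine course, and observation ends at a post-randomisation event that could differ between arms. Early deaths after discharge are left out, and the status of readmission deaths is unclear.

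The number of deaths affected cannot be derived from the protocol. It would be tempting to turn the 7 or 8 days into a share of early deaths missed, or into a spurious ratio between arms. Either would need an assumed mortality, an assumed pattern of deaths over time and assumed stays by arm, none of which the protocol gives. Such a figure would also overstate the loss if patients at highest risk remain in hospital.

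The primary outcome is not affected. This is a change that should be made, because it is cheap and removes a dependence on discharge. It does not call the main comparison of the trial into question.

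**What to change.** In section 5.2, add death from any cause within 30 days and within 90 days of surgery, for all randomised patients and regardless of discharge or readmission. For anyone randomised but not operated on, count from the day of randomisation. Keep in-hospital death beside it, and state whether it covers the first admission only or readmissions as well.

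In the Secondary outcomes text of the statistical section, set the comparison of 30- and 90-day mortality after the last patient has passed day 90. The comparison of complications and in-hospital death can stay at the last discharge. The chi-square or Fisher's exact test already listed will serve where day-90 status is complete. The Kaplan-Meier estimate at day 30 and day 90 covers any patient lost earlier.

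The cost is wording and a later short-term mortality comparison: day 90 instead of discharge on day 7 or 8 adds 82 to 83 days for a last patient with a routine course, or about three months. The dates of death are already collected for overall survival. The change touches outcome definition and analysis timing only, not discharge or any other part of patient care.

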**Primary outcome**

**Overall survival**, calculated from the time of randomization to death from any cause or the time to the last follow-up visit. Overall survival will be compared 3 years after the recruitment.

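### The primary completion date and the stated time of the overall survival comparison disagree by over two years, and the planned 80% power holds on only one reading of that time

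*Protocol*

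**What the plan says.** OS, counted from randomisation to death from any cause, is the sole primary outcome (Protocol, Section 5.1). The statistical analysis plan section of the protocol, under Primary outcome, sets its time: "Overall survival will be compared 3 years after the recruitment". Disease-free survival and recurrence are given the same time under Secondary outcomes.

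The date list under Section 4.3 gives a start of March 2013, a study completion of December 2019 and "Primary Completion Date: November 2016".

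Section 4.1 takes 5-year survival as 30% with two-field and 45% with three-field lymphadenectomy, and continues: "With a three-year accrual and an estimation of 10% loss of follow-up, 200 patients per study arm were necessary, using 80% statistic power". The test is the log-rank test, and a P "value of <0.05 is considered statistically significant".

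A separate item under Secondary outcomes reads: "Perioperative morbidity and mortality, and oncologic efficacy will be compared when the last patient discharged".

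**The concern.** A primary completion date normally marks the end of data collection for the primary outcome. A March 2013 start plus three years of accrual closes recruitment about March 2016, and three more years lead to about March 2019. November 2016 is only 8 months after that close. Both statements cannot describe the same OS analysis.

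The phrase that sets the OS time is itself open. Three years from the close of recruitment gives patients between three and six years of follow-up. Three years from each patient's entry gives everyone exactly three. These produce different numbers of deaths, and deaths determine the power of a log-rank test. In an open-label trial, a cut-off that can be read in several ways also leaves room to choose the analysis date after results by arm can be seen.

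**Working it through.** **Inputs from the protocol.** 5-year survival 30% and 45%, three-year accrual, 10% loss, 200 per arm and 80% power (Section 4.1); start March 2013 and primary completion November 2016 (date list under Section 4.3); significance level 0.05 and log-rank test (statistical section).

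**Assumptions not in the protocol.** Exponential survival, uniform accrual and a two-sided test. The form of the 10% loss is not stated, so results are given for 180 per arm (10% removed outright) and 200 per arm (no loss).

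**Reproducing the 200 per arm.** Two routes come close.
- Comparison of two proportions, 30% and 45%, with continuity correction: 176 per arm; 176/0.9 = 196.
- Log-rank test with 200 per arm, three years' accrual, three years' further follow-up and 10% loss per year: about 191 expected deaths and power 81% (Schoenfeld) or 80% (Freedman).

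The stated size is therefore credible for an analysis three years after recruitment closes.

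**Deaths needed.**
- Yearly hazards: λ = −ln(0.30)/5 = 0.2408 and −ln(0.45)/5 = 0.1597.
- Hazard ratio: 0.1597/0.2408 = 0.663; ln(HR) = −0.4106.
- Schoenfeld: D = 4(1.96 + 0.8416)² / 0.4106² ≈ 186.2, so 187 deaths for 80% power.

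**Deaths expected.** With accrual over a years and f further years, the fraction dying in an arm is 1 − [exp(−λf) − exp(−λ(a+f))]/(λa). When every patient is followed for exactly three years, it is 1 − exp(−3λ). Power = Φ(√D/2 × 0.4106 − 1.96).

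Example for a = 3, f = 3:
- Control: 1 − (0.4856 − 0.2358)/0.7224 = 0.654.
- Three-field: 1 − (0.6193 − 0.3836)/0.4791 = 0.508.
- With 180 per arm: D = 180 × (0.654 + 0.508) ≈ 209.
- Power = Φ(14.46/2 × 0.4106 − 1.96) = Φ(1.01) = 84%.

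| OS analysis time | Fraction dying (control / three-field) | Deaths, 360 to 400 patients | Power |
|---|---|---|---|
| 3 years after close of a 3-year accrual (about March 2019) | 0.654 / 0.508 | 209 to 232 | 84-88% |
| 3 years from each patient's entry | 0.514 / 0.381 | 161 to 179 | 74-78% |
| November 2016, accrual closed March 2016 | 0.394 / 0.286 | 122 to 136 | 62-67% |
| November 2016, accrual running to that date | 0.336 / 0.243 | 104 to 116 | 55-60% |
| 3 years after a 44-month accrual closing November 2016 | 0.678 / 0.531 | 218 to 242 | 86-89% |

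If the 10% loss is taken per year, Schoenfeld power is 81% in the first row, 73% in the second, 62% in the third and 55% in the fourth. The ordering and the conclusion do not change.

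**The case against.** The strongest defence is that November 2016 is not a planned OS analysis at all. The protocol attaches no comparison to that date. If it is the end of enrolment, three years later is November 2019, which fits the December 2019 study completion, and power is about 86-89%. This is plausible, and it means the 55-67% figures show what the labelled date would imply, not what the sponsor necessarily intends. It does not remove the contradiction: the date would then be mislabelled, and accrual would be 44 months against the three years in Section 4.1.

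It is also fair to say that the stated sample size works at the most natural reading, three years after close, and that the per-patient reading falls only modestly short.

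Three stronger readings may tempt a reader, and the protocol supports none of them.
- **Last discharge as a further OS date, and so an unadjusted interim look.** That time belongs to perioperative outcomes and oncologic efficacy, in a secondary item. OS, disease-free survival and recurrence each have their own three-year time. The fault there is that oncologic efficacy is not a listed outcome and is not defined.
- **Incomplete 5-year follow-up as a defect.** The log-rank test uses all deaths, and the 5-year rates may serve only to set the hazard ratio.
- **A need for a minimum number of deaths before analysis.** On the protocol's own assumptions 209 to 232 deaths are expected three years after close, above the 187 needed, so such a condition would not be expected to bind.

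**Conclusion.** The concern stands as an internal inconsistency in the timing of the sole primary test. The primary completion date of November 2016 does not fit an OS comparison three years after recruitment, and the starting point of those three years is not fixed. Of the three candidate times that follow from the stated dates and three-year accrual, only three years after recruitment closes reaches the planned 80% (84-88%). Three years per patient gives 74-78%, and November 2016 gives 55-67%, which is 51 to 83 deaths short of 187 (187 − 136 and 187 − 104). If November 2016 is the end of enrolment, power is adequate, but the date label and the accrual period still need correcting.

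The figures rest on exponential survival, uniform accrual, a two-sided 0.05 test and 360 to 400 contributing patients. The conflict between the dates rests only on the protocol's text.

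**What to change.** - **Primary outcome (statistical section):** state that OS is compared once, three years after the last randomisation, with survivors censored at that common cut-off.
- **Secondary outcomes:** use the same starting point for disease-free survival and recurrence.
- **Date list under Section 4.3:** change the primary completion date to that cut-off. If November 2016 is the end of enrolment, label it so, and reconcile the accrual period with Section 4.1.
- **Item tied to last discharge:** replace oncologic efficacy with the pathological measures available at discharge, such as node yield and margin status, so that it cannot be read as an early survival comparison. Section 4.4 already provides for recording margins and labelling nodes by site.

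The cost is wording and one corrected date. The primary readout is dated later than November 2016, but within follow-up already planned: the follow-up section schedules visits through the fifth year and annually after that.
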